**Acceptability:**

- Participants attending ≥ 70% of the sessions (5 out of 7 individual sessions).
- Estimate the rate of agreement/no agreement as to whether the MHELW think in their opinion that each session of the intervention was delivered as intended
- Estimates of failures to recruit due to lack of acceptability, participants dropped out due to lack of acceptability, and adverse or serious adverse events.

***All assessment schedules intended for use in the definitive trial will be used in this feasibility pilot study. These are:***

***Intended primary outcome: work productivity (measured at baseline and 3 months)***

This will be measured by the Work Productivity and Activity Impairment: General Health v2.0

(WPAI:GH) scale [22]. The WPAI-GH consists of 4 metrics: absenteeism (the percentage of work time missed because of one’s health in the past 7 days), presenteeism (the percentage of impairment experienced while at work in the past 7 days because of one’s health), overall work productivity loss (overall work impairment measured by combining absenteeism and presenteeism to determine the total percentage of missed time), and activity impairment (the percentage of impairment in daily activities because of one’s health in the past 7 days). The WPAI has been shown to demonstrate good internal consistency. This study will focus on the work productivity items of the WPAI-GH. Presenteeism (percentage of impairment experienced while at work in the past seven days due to health problems), absenteeism (percentage of work time missed due to health problems in the past seven days), overall impairment (combination of absenteeism and presenteeism). The WPAI-GH outcomes are expressed as impairment percentages, with higher numbers indicating greater impairment and less productivity. The WPAIGH contains the following six questions with a recall period of the last week: Q1=currently employed; Q2=hours missed due to health problems; Q3=hours missed due to other reasons; Q4=hours actually worked; Q5=degree health affected productivity while working; and Q6=degree health affected regular activities. Absenteeism is defined as the percentage of time absent from work due to health of the last week and is calculated by the formula Q2/(Q2+Q4) ×100%. Presenteeism is measured by the degree health problems affected work productivity of the last 7 days on a rating scale ranging from 0 to 10, with 0 indicating that health problems had no effect on my work and 10 indicating that health problems completely prevented me from working. The outcome is expressed as a percentage score representing the impairment due to health reasons while working, with higher numbers indicating greater impairment and less productivity, and is calculated by the formula (Q5/10) ×100%.

***Intended secondary outcomes (measured at baseline and 3 months): Employee***

1. **Job satisfaction**

Measured using the Indiana Job Satisfaction Scale which is a brief job satisfaction questionnaire designed for use with individuals with a severe mental illness. The IJSS consists of a 32-item self-report questionnaire, divided into six subscales: ‘*General Satisfaction’*, ‘*Pay*’, ‘*Advancement and Security’*, ‘*Supervision*’, ‘*Co-workers’* and ‘*How I feel about this job’*. The IJSS shows high internal consistency (α = 0.90) and test-retest reliability (r = 0.75) [23].

1. **Anxiety**

Anxiety is measured using the General Anxiety Disorder-7 [24]. The GAD-7 is commonly used in primary care and mental health settings as a screening tool and symptom severity measure. Using the threshold score of 10, the GAD-7 has a sensitivity of 89% and specificity of 82%, with high test-retest reliability (ICC = 0.83). Higher GAD-7 scores have been shown to correlate with disability and functional impairment [25]. A score of 5-9 indicates only mild GAD and suggests monitoring these individuals, 10-14 identifies moderate GAD symptoms and describes a possible clinically significant condition, whilst scores above 15 indicate severe GAD symptoms and advises for active treatment.

1. **Depression**

The severity of depression is measured using the Patient Health Questionnaire-9 [26]. The PHQ-9 assesses the severity of depression across the nine DSM-IV criteria on a 0-3 Likert scale. The scale has been validated for use in primary care [27]. The PHQ-9 has been shown to identify depression in at risk populations [28]. A criterion score of ≥10 has been shown to have an 88% and a specificity of 88% for major depression [26]. Scores of 0-4 denote no clinically significant symptoms; scores between 5-9 denote subthreshold symptoms; scores of 10-14 indicate moderate symptoms (below clinical thresholds); scores of 15-19 indicate moderately severe (above clinical thresholds) whilst scores of 20-27 indicate severe symptoms (above clinical threshold).

1. **Health-related quality of life**

The health-related quality of life is measured using the Euro-QoL-five-dimensional scale [29]. The EQ-5D 5L consists of 6 items stemming across: ‘Mobility’, ‘Self-care’, ‘Usual activities’, ‘Pain / discomfort’, ‘Anxiety / depression’ and ‘health today’. The scale has shown to demonstrate reliable test-retest effects (ICC > 0.7), and significant concurrent validity (rs ≥ 0.44).

1. **Sense of control**

It is understood that well-being indexes (for example depression and health) are associated with a perceived sense of control [30-32]. The Sense of Control scale is a two-dimension scale consisting of a total of 12 items [30]. The Sense of Control scale consists of ‘Personal Mastery’ and ‘Perceived Constraints’. The scale demonstrates good internal consistency (α = 0.86 Perceive Constraints; α = 0.70 Personal Mastery).

1. **Decisional conflict**

Employee and manager decisional conflict [33]: Decisional Conflict Scale: a 16-item scale designed to measure personal perceptions of uncertainty in choosing between options, modifiable factors contributing to uncertainty including feeling uninformed, lack of clarity about personal values and feeling unsupported in decision making, effective decision making such as feeling the choice is informed, values-based, likely to be implemented and expressing satisfaction with the choice

1. **Days taken on sick leave in the last month (self-reported by employee)**

***Intended secondary outcomes (measured at baseline and 3 months): Line Manager***

1. **Mental Health Knowledge.**

Knowledge about mental health will be assessed using the 12-item Mental Health Knowledge Schedule [34]. The scale of the MAKS ranges from 1 (Strongly Agree) to 5 (Strongly Disagree); an example item is “Most people with mental health problems want to have a paid employment.” The scale shows good item retest reliability from 0.57 to 0.87.

1. **Personal stigma.**

Attitudes about mental health will be measured using a modified version of the 9-item Personal Depression Stigma Scale [35]. The scale will be modified by replacing the word “depression” with the term “mental health problem.” The scale ranges from 1 (Strongly Agree) to 5 (Strongly Disagree). The scale shows good internal consistency (α = 0.76).

1. **Self-efficacy**

Managers’ self-efficacy surrounding mental health will be measured using an adapted version of the 9-item General Self-Efficacy Scale [36]. Items will be adapted to reflect self-efficacy related to employee mental health. The scale ranges from 1 (Strongly Disagree) to 6 (Strongly Agree) and includes the item “I feel confident about promoting employee mental health.” Reliability ranges from 0.76 to 0.90.

1. **Promotion intentions.**

Managers’ intentions to promote mental health in the workplace will be measured using an adapted version of a safety scale designed to assess managers’ safety promotion intentions [37]. The measure consists of three items: “It is very likely that I will promote mental health in my workplace,” “I intend to achieve the performance-based goals that I set for myself,” and “I want to apply what I learn about mental health to my work setting.” The scale ranged from 1 (Strongly Disagree) to 6 (Strongly Agree).

1. **Burnout.**

The Shirom-Melamed Burnout Measure [38] will be used to measure job-related burnout. This well-established 14-item scale has three subscales that are designed to capture core components of the burnout syndrome: physical fatigue, emotional exhaustion, and cognitive weariness. We selected this particular measure for the following reasons: (1) its theoretical underpinnings are clearly specified; (2) it explicitly seeks to capture a construct that is distinct from depression and anxiety; and (3) unlike more generic burnout measures, responses to the SMBM are temporally anchored to the past 30 workdays.

1. **Work performance.**

Work performance will be measured with the IWPQ [39]. This scale consists of three scales: task performance, contextual performance and counterproductive work behaviour) with a total of 18 items. Each subscale ranges between 0 and 4.

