**Role descriptors of the MHELW:**

These are based in part on the Individual Placement Support (IPS) employment specialists and the IPS fidelity scale [16], but with modifications and specifications aimed at supporting people already in employment to maintain this and improve their well-being. These have been developed and refined by Mind (the provider organisation) subsequent to internal Mind stakeholder consultation groups. These descriptors are:

1. An ethos that recovery is likely and therefore work can be maintained

1. Zero exclusion – a person’s desire to continue to be employed is the only criterion for access to the MHELW.
2. The support provided will be based on employee preferences
3. The MHELW will work independent to the business and employee but will focus on both sets of needs-this is based on the idea that it is in the interests of both the business and employee that the individual be supported to continue to work, and their experience of work be improved
4. The support to the business and employee will be individually tailored but will in general terms involve stage 1 (preparatory meetings with both parties where process and desired outcomes are explored), stage 2 (involving tailored support regarding adaptations, education, mental health support), and stage 3 (review of actions and impacts and future planning)
5. Acting as main point of liaison between NHS providers, the business (line manager) and employees subject to consents. In practice this may involve attending joint meetings between the employee and manager or holding individual meetings and advising on what adaptations might be necessary for the worker and supporting these to happen. It may also involve providing feedback to care providers in the form of a report on progress made and topics covered during the intervention, as well as background on the participant’s workplace context (subject to consent).
6. from the business (subject to consent)
7. Monitoring and reviewing adaptations
8. Upskilling the business line manager and employees about the importance of work for mental health by providing relevant mental health education
9. Providing basic mental health support to employees, but not any formal therapy as this might interfere with their current NHS treatment plan
10. High accessibility of help-links with employer platforms, posters, emails sent to staff
11. MHELWs will have initial group training and ongoing group supervision

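### Item 2 of the managers' promotion-intentions measure asks about general performance goals, so one of its three items is off the stated construct

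*Protocol*

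**What the plan says.** In the Protocol, the promotion-intentions entry under "Intended secondary outcomes (measured at baseline and 3 months): Line Manager" states the construct and the instrument: "Managers’ intentions to promote mental health in the workplace will be measured using an adapted version of a safety scale". It then prints three items, each rated from 1 to 6:

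- Item 1: "It is very likely that I will promote mental health in my workplace"
- Item 2: "I intend to achieve the performance-based goals that I set for myself"
- Item 3: "I want to apply what I learn about mental health to my work setting"

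Table 1 carries the measure as a single line, completed by line managers at baseline and 3 months. The protocol gives no scoring rule, no reliability figure for this measure and no reason for item 2. The Data analysis plan compares outcome measures between arms with a time-by-condition ANOVA. The Acceptability section says that every assessment meant for the definitive trial is used in this study.

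**The concern.** The outcome is named as an intention to promote mental health, but item 2 asks only whether managers mean to reach performance goals they have set for themselves. A manager thinking solely of commercial targets could give the highest rating without any intention to promote mental health.

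The wording also departs from how the same section treats its neighbouring scales. The stigma scale has its key term replaced so that it refers to mental health problems, and the self-efficacy items are to be adapted to employee mental health. The promotion scale is likewise called adapted, and items 1 and 3 carry that content. Item 2 does not.

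What is at stake is the preliminary estimate for this outcome and the choice of measure for the definitive trial. If item 2 is averaged in and does not move with the intervention, the score understates any change in the intention that it is named for.

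**Working it through.** **Item content**

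| Item | Names mental health | Names promoting or applying it at work |
|---|---|---|
| 1 | yes | yes |
| 2 | no | no |
| 3 | yes | yes |

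This comparison establishes the defect without any arithmetic.

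**Possible size**

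The protocol gives no effect, reliability or sample size for this outcome, so it has no figure to reproduce. The following is an illustration, and every input is an assumption:

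- the score is the simple mean of the items;
- each item has SD 1;
- the intervention shifts items 1 and 3 equally, by one unit;
- it does not shift item 2;
- r is the correlation between items 1 and 3, taken as 0.5 to 0.6;
- q is the correlation of item 2 with each of the others, taken as 0 to 0.4.

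Formulas:

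- Items 1 and 3 only: the shift is 1 and the variance of the mean is (1 + r)/2, so d₂ = 1/√[(1 + r)/2].
- All three items: the shift is 2/3 and the variance of the mean is (3 + 2r + 4q)/9, so d₃ = (2/3)/√[(3 + 2r + 4q)/9] = 2/√(3 + 2r + 4q).

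| r | q | d₂ | d₃ | d₃/d₂ |
|---|---|---|---|---|
| 0.5 | 0 | 1.155 | 1.000 | 0.87 |
| 0.5 | 0.2 | 1.155 | 0.913 | 0.79 |
| 0.5 | 0.4 | 1.155 | 0.845 | 0.73 |
| 0.6 | 0 | 1.118 | 0.976 | 0.87 |
| 0.6 | 0.4 | 1.118 | 0.830 | 0.74 |

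Worked line for r = 0.5, q = 0.4: d₃ = 2/√(3 + 1.0 + 1.6) = 2/√5.6 = 0.845; d₂ = 1/√0.75 = 1.155; ratio 0.845/1.155 = 0.73.

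**Sensitivity**

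Over wider correlations (r from 0.3 to 0.7, q from 0 to 0.6):

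- item 2 does not respond: ratio 0.66 to 0.88;
- item 2 responds half as much as the others (shift 2.5/3): ratio 0.82 to 1.10;
- item 2 responds fully (shift 1): ratio 0.99 to 1.32.

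The result depends chiefly on whether item 2 responds, and the protocol does not say.

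**The case against.** The best defence is that two of the three items do address the construct, the source scale is not at hand, and scoring may be left to an analysis plan that is not shown. The items might never be averaged. The study states that it does not test hypotheses, and none of its feasibility or acceptability criteria uses this score. All of this stands, and it limits how much the point matters. It does not change the printed wording of item 2, which a scoring rule would not repair.

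A reader might infer more than the protocol supports:

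- *The measure fails to capture its construct.* Items 1 and 3 both concern mental health at work, so the defect lies in one item.
- *Any effect is diluted.* That holds only if item 2 is combined with the others and does not respond.
- *Item 2 was left unadapted from the safety scale.* The items of the source scale are not available, so this cannot be known.
- *Item 3 is also faulty because it presupposes learning.* The role descriptors do include "Upskilling the business line manager and employees about the importance of work for mental health by providing relevant mental health education", and control managers receive the intervention only after the 3-month assessment. Yet the item can be answered prospectively and is not confined to what the trial teaches. Employers in the study are also briefed and given information beforehand. Education in one arm could widen the difference on this item as easily as blur it. At most this is something to bear in mind when interpreting arm differences.
- *The definitive trial would need a larger sample.* Squaring the worst ratio above gives 1/0.732² = 1.87, but the protocol's full-trial sample size concerns work productivity. No sample size rests on this outcome.

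**Conclusion.** The point holds in a narrow form. As printed, item 2 is about general personal performance goals, so one of three items does not belong to the stated construct, and the protocol gives no reason for including it. The consequence is conditional. With simple averaging, equal SDs, no response on item 2 and correlations in the assumed range, the score keeps about 0.73 to 0.87 of the standardised effect on items 1 and 3. If item 2 responds, the attenuation shrinks and may vanish. The protocol does not settle which case applies.

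The weight is low: this is one of six intended line-manager secondary outcomes in a feasibility study. It is worth correcting because the same measure is meant for the definitive trial.

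**What to change.** Tie item 2 to the construct, for example: *I intend to achieve the goals that I set for myself for promoting mental health in my workplace.* Item 3 needs no change.

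If the questionnaire is already in use, keep the wording so that baseline and 3-month answers remain comparable. Report item 2 separately from items 1 and 3, and check internal consistency before carrying the measure into the definitive trial. With only 56 participants planned, that check will be imprecise, so item content should weigh in the decision as well.

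The cost is one item wording in the online questionnaire, or a few extra lines of reporting. The downside of rewording is slightly less comparability with the source scale, which the protocol already describes as adapted.

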**Table 1: Data collection process and timepoint**

| **Measured outcome** | **Data collection method** | **Assessment method** | **Measurement timepoint** | | **By whom** |
| --- | --- | --- | --- | --- | --- |
|  |  |  | **Baseline** | **3 months** |  |
| Work productivity | Work Productivity and Activity Impairment: General (WPAI-GH) | Online questionnaire via Qualtrics | [figure not shown] | [figure not shown] | Employee (self-report) |
| Job satisfaction | Indiana Job Satisfaction Scale | Online questionnaire via Qualtrics | [figure not shown] | [figure not shown] | Employee (self-report) |
| Anxiety | General Anxiety Disorder-7 | Online questionnaire via Qualtrics | [figure not shown] | [figure not shown] | Employee (self-report) |
| Depression | Patient Health Questionnaire- 9 | Online questionnaire via Qualtrics | [figure not shown] | [figure not shown] | Employee (self-report) |
| Health related quality of life | Euro-QOL – five-dimension scale | Online questionnaire via Qualtrics | [figure not shown] | [figure not shown] | Employee (self-report) |
| Sense of control | Sense of control scale | Online questionnaire via Qualtrics | [figure not shown] | [figure not shown] | Employee (self-report) |
| Decisional deficit | Decisional Conflict scale | Online questionnaire via Qualtrics | [figure not shown] | [figure not shown] | Employee (self-report) |
| Days on sick leave | Self-reported employee sickness record | Survey via Qualtrics | [figure not shown] | [figure not shown] | Employee (self-report) |
| Mental Health Knowledge | Mental health knowledge scale | Online questionnaire via Qualtrics | [figure not shown] | [figure not shown] | Line manager (self-report) |
| Attitude about mental health | Personal depression stigma scale | Online questionnaire via Qualtrics | [figure not shown] | [figure not shown] | Line manager (self-report) |
| Self-efficacy | General self-efficacy scale | Online questionnaire via Qualtrics | [figure not shown] | [figure not shown] | Line manager (self-report) |
| Mental health promotion | Safety promotion intentions scale | Online questionnaire via Qualtrics | [figure not shown] | [figure not shown] | Line manager (self-report) |
| Burnout | Burnout scale | Online questionnaire via Qualtrics | [figure not shown] | [figure not shown] | Line manager (self-report) |
| Work demand | Individual work performance scale | Online questionnaire via Qualtrics | [figure not shown] | [figure not shown] | Line manager (self-report) |
| Number of eligible participants | Trial document (case report form) entry record | Password protected spreadsheet/Qualtrics | [figure not shown] |  | Research Fellow |
| Number recruited | Trial document (case report form) entry record | Password protected spreadsheet/Qualtrics | [figure not shown] |  | Research Fellow |
| Number consented | Trial document (case report form) entry record | Password protected spreadsheet/Qualtrics | [figure not shown] |  | Research Fellow |
| Number retained | Trial document (case report form) entry record | Password protected spreadsheet/Qualtrics |  | [figure not shown] | Research Fellow |
| Number of contacts of MHELW | Trial document (case report form) entry record | Password protected spreadsheet/Qualtrics |  | [figure not shown] | Record entered by MHELW |
| Length of contact of MHELW | Trial document (case report form) entry record | Password protected spreadsheet/Qualtrics |  | [figure not shown] | Record entered by MHELW |
| Number of contacts  between MHELW and NHS providers | Trial document (case report form) entry record | Password protected spreadsheet/Qualtrics |  | [figure not shown] | Record entered by MHELW |
| Referrals to non- statutory providers | Trial document (case report form) entry record | Password protected spreadsheet/Qualtrics |  | [figure not shown] | Record entered by MHELW |
| Semi-structured interviews | Face to face/telephone | Audio-recorded |  | [figure not shown] | Research Fellow |

1. **Data analysis plan**

Data analysis will be performed after the last trial participant has completed their 3-month post-intervention. Descriptive statistics (means, SDs, and medians) will be used to report recruitment, retention rates and efficacy outcomes measures (both primary and secondary). Baseline between-group differences will be tested by conducting independent sample t-tests between the intervention group and the control on outcomes measures. A 2 x 2 ANOVA - with Time as the within-subject variable (baseline and 3-month post-intervention) and Condition (MENTOR and control condition) as the between-subject variable – will be conducted to test whether outcome measures improved in the active condition relative to the control at the 3-month post-intervention time-point. Intervention adherence will be calculated by assessing the response rate of participants receiving the intervention, response rate of completed questionnaires, and the number of sessions completed by intervention group participants. Recruitment and dropout rates will be evaluated using absolute and percentage frequencies. Analyses will be performed using statistical software Stata (Stata, version. 16.0; Stata Corp) and SPSS version 24. The intention-to-treat (ITT) principle will be applied to the primary analyses with all participants’ data being analysed as per their assigned intervention at baseline. Following randomisation participants who withdrew consent or those with a protocol violation concerning eligibility will be excluded from the ITT analysis. Participants with missing baseline information and those who do not complete intervention or are lost to follow-up will be included in the dataset; multiple data imputation and sensitivity analyses will be performed. Summary statistics will be provided for all variables.

Data will be collected using online proforma, the pre-screen questionnaire will be administered using Qualtrics survey platform. All data collection of outcome measures and pre-screening scales are administered using the Qualtrics platform, with data stored on the Qualtrics servers in accordance with GDPR governance. Any notes that the MHELW makes will be uploaded and made anonymous in the same way. MHELW will be provided access to the Qualtrics platform using a unique identification code via the email address MHELW provides with a chosen password to upload any intervention notes.

1. **Process Evaluation**

The process evaluation will use a mixed method approach and use the RE-AIM (reach, effectiveness, adoption, implementation, and maintenance) framework [40]. It will be made up of two parts:

1. **Quantitative data collection:**

During the course of the study and at 3 months after baseline we will measure

- Number of contacts with MHELW
- Length of contacts of MHELW
- Number of contacts between MHELW and NHS providers
- Referrals to non-statutory providers

1. **Qualitative data collection:**

We will conduct a qualitative evaluation aiming to explore engagement, acceptability, barriers, and facilitators, for employees, line managers and MHELWs delivering the intervention. Participants who were selected and agreed to take part in the interview will be sent a consent form and participant information sheet via email. We will explore what have MHELW been asked to do, whether they feel able to complete these actions and what they have felt unskilled for. Qualitative data will be collected from sub- samples of these 3 stakeholder groups using either individual interviews or focus groups depending on acceptability to businesses and workers. These are:

1. Employees (N=16-20) individual interviews,
2. Line Managers (N=16-20) individual interviews
3. MHELWs (N=6-8)-focus group.

Participants will be purposively sampled to take account of sector, job role, seniority, age, gender, and those who completed the intervention. Three separate semi-structured interview schedules will be developed focused on exploring the main aims of the qualitative study. Some schedule components are likely to overlap. Interviews will be scheduled at a convenient time and location for the interviewee. Interviews will be audio-recorded on an encrypted device with consent and then subsequently transcribed verbatim. Any references and names to participants will be redacted using search and replace functions, all references to names will be replaced with randomly generated pseudonyms using <https://www.fakenamegenerator.com>. Recordings will be transferred from University of Warwick to the Research Data Store (RDS) on the University of Birmingham servers and deleted immediately from the recording device once this is safely transferred. The audio files will then be deleted once transcription is completed. A professional transcription service will assist in the transcription of the interviews. The transcriber will sign a Confidentiality Agreement and will comply with the data protection act. The anonymised interview transcript will be deleted after 10 years from RDS on the University of Birmingham servers. Interviews will be conducted face-to-face or by telephone/online. Microsoft Teams will be used to provide a video conference platform for the online interviews. However, due to the current COVID-19 pandemic and social distancing measures interviews may be conducted remotely (telephone/online). Furthermore, a purposeful sample of MHELWs will be invited via email to consider participating in a focus group interview at the end of the 3 months intervention to ensure a broad range of participant experiences is captured. Once, the MHELWs expressed an interest in participating, the same recruitment procedures will be followed, including sending an information sheet and a consent form to participate via email. It is possible that discussion about certain topic could be sensitive and upsetting that may results in distress or discomfort. It is possible that participants could disclose information requiring action. To minimise risks we will ensure that, (a) MHELWs receive adequate training in how to support participants and manage their discussions in a constructive manner; (b) any disclosures requiring action are passed on to the research team for action. It will be made clear to participants that they may withdraw consent at any point; (c) Participants are aware that they can choose to omit answering questions. Also, participants are free to withdraw from the trial at any time should they wish to on account of perceived intrusion/inconvenience.
